#### Recruitment of Study Participants

A convenience sample will be recruited. The following 5 early psychosis intervention sites will recruit the participants: London, Toronto, Hamilton, Ottawa, and Montreal. All early psychosis intervention sites share the same entrance criteria for admission and offer similar services. The sites provide a pool of over 1000 patients with a first episode of psychosis. Based on prior early intervention studies involving this population, at least 30% will be of Black African and Caribbean descent [37,39]. Staff at each site will receive training about recruitment, approach eligible clients, and obtain consent for the research coordinator to contact them. Participants can access laptops on loan from the study or, when pandemic restrictions allow, can access computers at early intervention programs.

#### Data Collection

This phase of the project involves baseline clinical assessments. Research staff will conduct an individual interview to obtain baseline demographic/clinical measures and illicit narratives exploring the perceptions of the effects of cannabis use on psychosis (Figure 2).

**Figure 2 figure2:**
[figure not shown]
Study design. PCT: Psychosis and Cannabis Test.

#### Assessment

Demographic data will be collected on gender, sex, age, ethnicity, education, living circumstances, language, income, immigrant status (first or second generation), employment, disability status, and DSM-5 diagnoses.

#### Measures

##### Clinical and Sociodemographic Measures

The Diagnostic Assessment Research Tool (DART) for DSM-5 diagnoses [50] will be used as an interview guide to help establish the diagnosis. Baseline measures will also be drawn from demographic tools used in the Ontario Community Mental Health Evaluation Initiative [51]. This tool collects information on marital status, ethnicity, employment status, immigration status, and other sociodemographic characteristics.

##### Drug Use and Abuse

The prevalence rates of cannabis and alcohol use disorders will be assessed using the DART for lifetime and the 12-month period prior to the baseline assessments. The DART is an open-access semistructured interview developed by researchers at McMaster’s Department of Psychiatry and Behavioral Neurosciences for clinical and research assessments of DSM-5 diagnoses for mental disorders. The Schizophrenia and Substance Use Disorders modules will be adopted for this project [50].

##### Drug Abuse Screening Tool

The Drug Abuse Screening Tool (DAST) will be used to track cannabis use indicative of abuse before clinic registration and at 12 months. The DAST monitors drug use problems during the previous 12-month period. The DAST identifies drug abuse when a score of 6 or more is obtained. The lowest score is 0, and the highest score is 20 [52]. It has been used in previous studies to identify substance use disorder among young people with a first episode of psychosis [16].

##### Insight

The Birchwood Insight Scale will be completed. It contains items about illness awareness, symptom recognition, and the need for treatment. It has been validated in schizophrenia and patients with a first episode of psychosis [53].

The Cannabis Experience Questionnaire has been used to measure the intoxication effects of cannabis among cannabis users and has been validated with confirmatory factor analysis [54]. It has been used in early phase psychosis to track the frequency and THC content of cannabis use [55]. It assesses the frequency of use (every day, more than once a week, about once a week, about once a month, a few times each year, only once or twice, and never) [55]. It has been used in epidemiological studies involving first-episode psychosis participants in the United Kingdom to estimate the type of cannabis used. This aspect was developed by collecting data on the THC content of cannabis confiscated by police [56]. We have adapted it for the Ontario context by estimating THC content based on a Marketplace survey of products sold at dispensaries in Canada [57,58]. It includes the following question: What potency of cannabis do you/did you usually buy? (Indicate the most frequent if this varies). The response options are (1) Low potency, 5% or less (THC content labeled or hash oil); (2) Medium potency, 6%-14% (THC content labeled at a government-sponsored dispensary); (3) High potency, 15%-29% (most dispensaries not licensed by the government); (4) Extremely high potency, 30%-100% (synthetics, concentrates, shatter, dab, or spice). 

#### Analyses

##### Quantitative Analysis

Descriptive statistics (mean and standard deviation for normally distributed continuous variables, median for variables with skewed distribution, and frequency and percentage for categorical variables) will be used to depict the demographic and clinical characteristics and will explore the relationship between the variables of interest. Relevant tests of significance, including chi-square, correlation, and regression tests, will be performed.

### Visit 2: Perspectives on Cannabis and Psychosis

#### Research Questions

The primary research questions about the perceptions of cannabis and psychosis are as follows: How do young people with a first episode of psychosis and cannabis use disorder from Black racialized communities conceptualize the mental health impacts of cannabis on psychosis? How do gender and ethnicity influence the messages?

#### Study Population and Recruitment

See Visit 1: Baseline Assessments for criteria and procedures. The same participants will take part in this phase of the study.

#### Data Collection

##### Qualitative Interview

The research staff will ask participants to share their stories and perspectives involving cannabis and psychosis. Semistructured open-ended questions will be used to elicit narratives on mental health and cannabis use experiences. Stories will also be elicited about the age of first use, frequency of use, potency of products, choice of products, route of administration, and views on how gender or ethnicity influences cannabis use.

The interviews will be recorded and transcribed verbatim. The Sex- and Gender-Based Analysis Plus will be used to ensure the data are collected and analyzed in a manner sensitive to gender (sociocultural) and to integrate factors, such as race, language, age, immigration, or disability [59]. The research staff will explore within-group themes that are contextually grounded in the following: (1) race and ethnicity as social constructs (for example, Black African versus Black Caribbean), (2) gender (men/transmen versus women/transwomen versus fluid/nonbinary/two-spirit), (3) immigration status (first or second generation), and (4) study site (for example, Montreal versus London to capture variations based on geography).

#### Qualitative Analysis

The data will be thematically analyzed as described by Braun and Clark [60]. The research staff will conduct thematic analysis, code and label data extracts, and search for phrases and imagery related to cannabis and psychosis, focusing on different perspectives based on gender and ethnicity. This analysis will be presented to the advisory council to help formulate meaning from the data and to help create visual models of the constructs.

#### Sample Size

Twelve or more participants from each of the 2 ethnic groups and the 2 largest gender groups should be sufficient to reach saturation of the perspectives for each group by the third visit. Saturation has been shown to occur within the first 12 interviews within a group [61].

### Visit 3: Gameplay and Knowledge Transfer

#### Research Questions

The research questions are as follows: (1) How do the themes about cannabis and psychosis change after playing the Back to Reality Series? (2) What is the game’s impact on knowledge acquisition about cannabis and psychosis?

#### Hypothesis

We hypothesize a significantly greater knowledge test score (>18%) in the group first exposed to the Back to Reality Series compared to the control game. We expect this finding for Black African and Black Caribbean groups, Black men, Black women, and all ethnic groups with a first episode of psychosis and cannabis use disorder.

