##### Quantitative Analysis

We will compare the performance of the groups on the PCT Quiz using the *t* test. A minimum difference of 18% in PCT Quiz scores represents a statistically and meaningfully significant increase in knowledge, based on a pilot study [45].

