#### Sample Size

Based on pilot data involving 10 participants with a first episode of psychosis, the mean baseline score was 6.5 (SD 1.3). The effect size is 1.17 (18% × 6.5) to detect a difference of 18%. The standardized effect size (E/S) is 0.9 (1.17/1.3 [effect size/SD]). The power calculations [64] suggest that 20 participants are sufficient per group. With a minimum of 24 participants per gender and racialized group at visit 1, there would be at least 20 participants per group by visit 3 (up to 4 weeks later), with a projected dropout rate of 15%.

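### A significant quiz-score gain is expected in each of four Black subgroups as well as overall, but each subgroup has only about 10 v 10 participants and about 48% power

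*Protocol article*

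**What the plan says.** All references are to the protocol article.

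- **Visit 3, Hypothesis.** The lead sentence is overall and directional: "We hypothesize a significantly greater knowledge test score (>18%) in the group first exposed to the Back to Reality Series compared to the control game". The next sentence extends it to five overlapping groups: "We expect this finding for Black African and Black Caribbean groups, Black men, Black women, and all ethnic groups".
- **Visit 3, Quantitative Analysis.** A t test is named: "We will compare the performance of the groups on the PCT Quiz using the" (end of sentence omitted here). The section does not say whether the groups are the two game-order arms, the subgroups, or both. It treats an 18% difference as the smallest that counts as both statistically and practically significant.
- **Visit 3, Sample Size.** The pilot values are stated first: "the mean baseline score was 6.5 (SD 1.3"). From these comes the target difference: "The effect size is 1.17 (18% × 6.5) to detect a difference of 18"%. It is next standardized: "The standardized effect size (E/S) is 0.9 (1.17/1.3 [effect size/SD"]). The section concludes that "20 participants are sufficient per group" and applies this number to subgroups: "With a minimum of 24 participants per gender and racialized group at visit 1, there would be at least 20 participants per group by visit" (the third visit is meant), allowing for 15% dropout.
- **Visit 1, Study Population.** 24 Black African, 24 Black Caribbean and 24 participants of any ethnicity, with equal numbers of men and women in each racialized group.
- **Visit 3, Data Collection and Procedures.** The game played first is randomized 1:1, and the quiz is taken after that first game.

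None of the five comparisons is labelled primary. Alpha, sidedness and power are not stated.

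**The concern.** The Hypothesis section treats significance in the four Black subgroups as an expected result on a par with the overall one, and the Sample Size section sizes the study for those subgroups. Subgroup testing is thus a design target and not an exploratory extra. The sized group is, however, split in two by the randomization, so each subgroup test has about half the participants that the calculation needs.

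At that size, significance in any one subgroup is close to a coin toss even if the game works equally well in all of them. A report that the game raised knowledge in one Black community but not in the other would be a likely chance result. It would bear directly on the question of ethnicity and gender that motivates the study. Setting one p-value beside another does not test whether effects differ.

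**Working it through.** **Inputs.** Difference 1.17 and SD 1.3 (Sample Size); 24 per ethnic group with equal men and women, hence 24 Black men and 24 Black women (Study Population); 15% dropout (Sample Size); 1:1 game order (Data Collection and Procedures). Assumed because unstated: two-sided 0.05 and 80% power. The fifth group, all ethnic groups, is taken as all participants pooled.

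**1. The plan's own figure.** n per arm = 2 × (1.96 + 0.84)² / 0.9² = 19.4, so 20 (20.4 with the exact t distribution). Dropout: 20 / 0.85 = 23.5, so 24. The stated 20 and 24 are reproduced, but as numbers **per game-order arm**.

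**2. What each subgroup has.** 24 × 0.85 = 20.4 at visit 3; 20.4 / 2 = 10.2 per arm, about 10 v 10. All participants: 72 × 0.85 = 61.2, about 30 v 30.

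**3. Power for a true 1.17-point effect.**

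| Comparison | Per arm | Power (exact t) |
|---|---|---|
| Each named Black subgroup | 10 | 47.8% |
| Same, with no dropout | 12 | 55.9% |
| Both Black groups combined | 20 | 79.2% |
| All participants | 30 | 92.9% |

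The smallest difference that is significant at 10 v 10 is 2.10 × 1.3 × √(2/10) = 1.22 points. That is above 1.17, so an observed 18% difference with SD 1.3 would not be significant in a subgroup.

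**4. Black African v Black Caribbean.** The two groups do not overlap. With p = 0.478 in each, P(exactly one significant) = 2 × 0.478 × 0.522 = 49.9%. Variants:

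- no dropout (12 v 12): 49.3%
- one-sided tests at 0.05: 47.5%
- SD 1.04, 1.6 or 1.9 (values in the article's account of pilot work): 45%, 45% and 38%
- 20 per arm in each subgroup: 33%

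**5. All five together.** Simulation of 200,000 trials: 3 ethnic strata × 2 genders × 2 game orders × 5 participants, normal scores, five t tests.

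- True effect 1.17 everywhere: all five significant in 15.6% of trials (27.8% if one-sided at 0.05).
- No effect anywhere, two-sided 0.05: at least one of five significant in favour of the Back to Reality Series 9.5%; in either direction 18.6%. A single test gives 2.5% in the favourable direction.
- No effect, other rules: one-sided 0.05, any group 17.2%; favourable, significant and observed difference at least 1.17, any group 5.6%; all five required, about 0.02%.

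**6. Interaction.** The standard error of the difference between two subgroup effects is 1.3 × √(4/10) = 0.82. Power to detect a difference in effect as large as 1.17 is Φ(1.17/0.82 − 1.96), about 30%.

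**The case against.** The strongest reply is that little here is written down as a decision rule. In the Quantitative Analysis section, the groups may mean only the two game-order arms. The lead sentence of the Hypothesis section can serve as the main test, and contrasts between communities are assigned to the qualitative work. Multiplicity rules and interaction terms are commonly left to a statistical analysis plan, which is not shown. The study is also framed as a feasibility evaluation.

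Much of this stands. Separate t tests are inferred, and the absence of an adjustment or an interaction term is not by itself a fault of the article. Three stronger readings are tempting but not supported:

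- **A false-positive risk of about 18%.** This counts results in either direction and needs a rule that any one group suffices. No such rule is stated, the hypothesis is directional, and its wording can equally be read as expecting the result in every group. With the any-group rule the risk in the hypothesized direction is about 9.5%, and 5.6% if the observed difference must also reach 18%.
- **Contradictory results in the two Black groups.** The 50% means that one is significant and the other is not. That reflects low power, not opposite findings.
- **Near-certain failure if all five must succeed.** The chance of success is about 16%: poor, but not nil.

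It could also be argued that 24 are meant in each gender-by-race cell, which would give about 20 per arm in each ethnic group. The Study Population section rules this out by fixing 24 per ethnic group.

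The reply does not remove the stated expectation of significance in the named subgroups, or the sizing that leaves each at about 10 v 10.

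**Conclusion.** The point holds as one of subgroup power and interpretation. With two-sided 0.05, SD 1.3 and a true 1.17-point effect everywhere, each named Black subgroup has about 48% power, the full set of expectations is met about 16% of the time, and the Black African and Black Caribbean results differ in significance about half the time. The last figure stays between 38% and 50% over the SDs and sidedness tried at 10 v 10.

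Inflated type I error is a secondary and conditional matter: about 9.5% against 2.5% for one test, and only if any single group counted as success. The overall comparison is sound, with about 93% power for significance. If the observed difference also had to reach 1.17, that would fall to about 50%, so the 18% should be used as the planning difference and not as an added hurdle.

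**What to change.** 1. Name the all-participant comparison of quiz scores by first game played as the single primary test. It matches the lead sentence of the Hypothesis section and is better powered than the combined Black groups (about 93% v 79%).
2. Reword the second sentence of the Hypothesis section along these lines: *The effect will be estimated, with 95% confidence intervals, in Black African, Black Caribbean, Black men and Black women participants; no significance claim will be made for any subgroup on its own.*
3. Examine whether the effect differs by racialized group and gender in one linear model with arm-by-group and arm-by-gender interaction terms. Report these as exploratory, because their power is low (about 30% even for a 1.17-point difference in effect).
4. State alpha and sidedness, and say in the Sample Size section that 20 is the number per game-order arm.

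The cost is wording and a slightly fuller model. No extra participants are needed. The sponsor gives up stand-alone subgroup significance claims.

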#### Study Population and Recruitment

See Visit 1: Baseline Assessments for criteria and procedures. The same participants will take part in this phase of the study.

#### Study Design

This study phase involves quantitative and qualitative components to establish the feasibility of knowledge acquisition through gameplay involving the Back to Reality Series. Knowledge acquisition will be measured using scores on a quiz, and changes in insight will be gleaned from qualitative inquiry into changes in perceptions about cannabis and psychosis before and after playing the game.

#### Data Collection and Procedures

The video games will be streamed over Zoom by the research staff. Participants will be randomized to determine the gameplay order (either the Back to Reality Series or the control game will be played first). A software program embedded within the download of the Back to Reality Series randomly assigns the order in which each participant plays the first game on a 1:1 basis. The randomization is not to allocate participants into groups. The experimental and control games are packaged on the screen to protect the blinding at the outset. However, the video games are not associated with preconceived notions of therapeutic benefit, which minimizes bias. The video games are password protected, so participants will not have had prior access.

Subsequently, participants will complete a quiz measuring factual knowledge about the impact of cannabis on psychosis. Participants are randomized so that differences in quiz scores can be attributed to gameplay interventions, which is an advantage over pre-post gameplay designs for quantitative analysis. This process also avoids having participants complete the same or similar quiz twice in a day. The research staff will conduct the knowledge test by displaying the questions to the participants and reading out each item. After completing the quiz, participants will immediately play whichever game remains. Thus, if the participant was randomized to play the Back to Reality Series first, the control game, Morpheus’ Spell, will subsequently be played.** **Each participant will complete a gameplay survey about the Back to Reality Series. Finally, participants will undergo a second qualitative interview to discuss ideas and impressions from their gameplay experiences and reflect upon their views about the relationship between cannabis and psychosis after playing the game.

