### Visit 1: Baseline Assessments

#### Study Population

The eligibility criteria are as follows: (1) meet the criteria for a first episode of psychosis defined as the first illness episode involving psychosis symptoms; (2) meet DSM-5 (Diagnostic and Statistical Manual of Mental Disorders, 5th Edition) criteria for a psychotic disorder and a lifetime or current cannabis use disorder (up to 45% of people with a first episode of psychosis will meet the criteria for cannabis use disorder [16,47,48]; patients diagnosed with cannabis-induced psychosis by definition meet the criteria for both conditions [49] and will be eligible); (3) be between the ages of 16 and 30 years; (4) self-identify as a Black African or Black Caribbean first- or second-generation immigrant (English speaking), or belong to any ethnic group; (5) be a client of an early psychosis intervention with up to 12 months of service; and (6) be fluent in English.

Participants will self-identify and be divided into the following disaggregated ethnic and racialized groups: Black African (n=24), Black Caribbean (n=24), and any ethnicity (n=24). There may be significant differences in social and community norms for cannabis use between Black African and Caribbean groups and differences in English proficiency, educational attainment, and immigrant status. Sex will be defined based on sex assignment at birth. Gender will be self-assigned as man, woman, transgender, fluid, two-spirit, and non-binary. Equal numbers of men (including transmen) and women (including transwomen) will be enrolled for each racialized group. Participants will self-identify as nonimmigrant, or first- or second-generation immigrant.

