#### Data Collection

##### Gameplay, Quantitative Test, and Qualitative Inquiry

This section will take 60-120 minutes. Each participant will be provided with a link to download the set of video games. A software program will randomly assign the order in which each participant plays the first game, the Back to Reality Series, or the control game on a 1:1 basis. It takes 45 minutes in total to play all the video games. Subsequently, the research staff will conduct the PCT Quiz by displaying the questions to the participants and reading out each item. Finally, the participants will play whichever game they had not played first.

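### Enrolment is fixed by racialized group and gender and the quiz effect is hypothesised in those groups, but no stratification or blocking of game order is described; stratifying would be a cheap gain in balance

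*Protocol article*

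**What the plan says.** All places are in the protocol article.

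- **Quotas (Visit 1, Study Population).** The groups are "Black African (n=24), Black Caribbean (n=24), and any ethnicity (n=24"), and "Equal numbers of men (including transmen) and women (including transwomen) will be enrolled for each racialized group". That makes 72 participants in six cells of 12. The same section says that Black African and Caribbean participants may differ in norms for cannabis use, English proficiency, educational attainment and immigrant status.
- **Hypothesis (Visit 3).** "We expect this finding for Black African and Black Caribbean groups, Black men, Black women, and all ethnic groups". Each named group is a quota group, a union of quota cells, or the whole sample.
- **Assignment (Visit 3, Data Collection and Procedures).** "A software program embedded within the download of the Back to Reality Series randomly assigns the order" of play, 1:1. The section Gameplay, Quantitative Test, and Qualitative Inquiry repeats this ("the Back to Reality Series, or the control game on a 1:1 basis") and adds: "Each participant will be provided with a link to download the set of video games". The first of these sections also says: "The video games will be streamed over Zoom by the research staff".
- **Analysis (Visit 3, Quantitative Analysis).** "We will compare the performance of the groups on the PCT Quiz using the" *t* test. No covariate is named. The quiz is taken once, after the first game, so there is no pre-game score.

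**The concern.** Racialized group and gender are recorded at Visit 1, and order is drawn at Visit 3. The factors are therefore known in time to balance on, yet the described mechanism makes no use of them. A self-contained program in a separate download would not ordinarily see earlier assignments or the player's stratum. Under such a mechanism 1:1 holds on average, and in groups of about 20 the realised split can be well away from it.

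Two things are at stake. Within a racialized group, an uneven split loses precision. In comparisons that pool over race or gender (all participants, Black men, Black women), the two orders can differ by chance in their mix. The article relies on randomization to attribute score differences to the game, and as written nothing in the analysis adjusts for that mix.

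**Working it through.** **Inputs.** Visit 3 Sample Size: mean 6.5, SD 1.3, difference 1.17, standardized effect 0.9, 20 per group, 24 enrolled with 15% dropout. Study Population: 24 per racialized group, half men and half women. Assumed because not stated: two-sided alpha 0.05, 80% power, and independent draws with probability 0.5.

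**1. The plan's own figure.** n per arm = 2(1.960 + 0.842)² / 0.9² = 2 × 7.85 / 0.81 = 19.4, so 20. Allowing for dropout, 20 / 0.85 = 23.5, so 24. Both figures reproduce, but the 20 is per arm, that is, per game order.

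**2. Chance of an uneven split.** X ~ Binomial(N, 0.5).

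| Group | Split or worse | Probability |
|---|---|---|
| 20 completers | 7:13 | 2 × 0.1316 = 0.263 |
| 20 completers | 6:14 | 0.115 |
| 24 enrolled | 8:16 | 0.152 |

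At least one of the Black African and Black Caribbean groups at 7:13 or worse: 1 − (1 − 0.263)² = 0.457. At least one of the three racialized groups of 24 at 8:16 or worse: 1 − (1 − 0.152)³ = 0.389.

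**3. What the split costs within a group.** Noncentral *t* power at d = 0.9, with noncentrality 0.9 × √(n₁n₂/(n₁+n₂)):

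| Split of 20 | Power |
|---|---|
| 10:10 | 47.8% |
| 7:13 | 44.3% |
| 6:14 | 41.5% |
| average over independent draws | 45.9% |

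The average loss is 47.8 − 45.9 = 1.9 points. At 7:13 the standard error rises by a factor √(1/7 + 1/13) / √(1/10 + 1/10) = 0.4688 / 0.4472 = 1.048, or 4.8%.

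**4. Mix of race or gender between orders.** Take 20 completers made of two subgroups of 10, such as men and women in one racialized group, or Black African and Black Caribbean men among Black men. With independent draws, the share of one subgroup differs between the two orders by 30 percentage points or more with probability 27%, and by 40 or more with probability 12%. If the subgroups differ by D points on the quiz, a 30-point difference in mix shifts the observed score difference by 0.3 × D. The documents give no D. Assuming D between half an SD (0.65) and one SD (1.3), the shift is 0.20 to 0.39 points, or 17% to 33% of the 1.17 targeted. It may fall in either direction.

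**The case against.** The strongest objection is that the absence of stratification is inferred. A reader might infer that the article says order is drawn without regard to race or gender. It does not say so. It says only that software assigns 1:1, and a condensed article may leave blocks or a server link to the full protocol. It is also unclear whether the participant or the staff runs the download. This stands as far as it goes: the supportable wording is that no stratification is described. Still, the mechanism is described twice, and independent draws are its natural reading.

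A reader might also infer that an uneven split biases the result. It does not. Under valid randomization, chance imbalance is not bias, and the standard error of the *t* test already allows for it. Within a single racialized group it cannot confound by race. Eligibility requires fluent English and the quiz is read aloud, which limits some of the differences named under Study Population, and that section says only that differences may exist.

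Third, the small race-by-gender cells give a more striking figure. With 10 per cell, 2:8 or worse has probability 2 × 56/1024 = 10.9%, and 1 − (1 − 0.109)⁶ = 50% for at least one of six. A reader might take that as the risk in the hypothesised groups. The hypothesis names none of those cells, so the figure does not carry the point.

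Finally, this phase is framed as feasibility work, and blocking lets staff who see the games guess some later orders. That second risk is real but minor, because participants are already enrolled when order is drawn.

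**Conclusion.** The point holds as a low-cost improvement and not as an error that invalidates the comparison. Enrolment and hypotheses are organised by racialized group and gender, and the described assignment does not use them. If draws are independent, a split of 7:13 or worse has probability 26% per racialized group of 20 completers, and 46% for at least one of the two Black groups. Within a group the cost is about 2 power points on average, 3.5 at 7:13 and 6.3 at 6:14. The unadjusted analysis also leaves uncorrected any chance difference in the mix of race or gender in the pooled, Black-men and Black-women comparisons.

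These figures rest on independent draws, 20 completers per group, d = 0.9 and two-sided alpha 0.05. A reader might infer that uneven splits explain the weak subgroup power. They do not: power is only 47.8% at a perfect 10:10, because the Sample Size section applies a per-arm 20 to groups that both orders share. That is a separate problem, and stratification would not repair it.

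**What to change.** 1. State how order is generated: whether draws are independent or blocked, and whether staff or the participant runs the download. Reconcile the two Visit 3 sections on this last point.
2. For participants not yet assigned, release the order at the start of Visit 3 from a concealed, pre-generated 1:1 list. Stratify it by racialized group and gender, with randomly varied block sizes, and include a stratum for participants outside the man/woman quotas. An unlock code in the existing game package would serve.
3. Include racialized group and gender as covariates in the pooled quiz comparison.

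No extra participants are needed. The cost is a small software or procedure change and entry of the stratum at each session. Staff who see the games could sometimes predict the next order, so block sizes and later list entries must stay concealed. Recruitment began in September 2021. Participants already assigned keep their order, so any imbalance already accrued remains; the covariates in step 3 would help with it in the pooled comparison.

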#### Measures

##### PCT

The PCT Quiz assesses relevant knowledge about the relationship between cannabis and psychosis. It takes about 10 minutes to complete and involves 10 multiple-choice questions worth 1-point each, with scores ranging from 0 to 10. The researchers will read the questions aloud to reduce the impact of reading literacy. The details are described elsewhere regarding the development of the quiz, and its reliability and validity [42].

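### The PCT Quiz is read aloud live by research staff who probably know which game was played first; keyed, displayed items limit the risk, and recorded, self-entered administration would remove most of it cheaply

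*Protocol article*

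**What the plan says.** The Visit 3 procedures (protocol article, Data Collection and Procedures) assign both tasks to the same category of staff. On the games: "The video games will be streamed over Zoom by the research staff". On the quiz: "The research staff will conduct the knowledge test by displaying the questions to the participants and reading out each item". The PCT section gives the reason for the live reading: "The researchers will read the questions aloud to reduce the impact of reading literacy".

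The session is continuous. The first game is played, the quiz follows, and then: "After completing the quiz, participants will immediately play whichever game remains". Software "randomly assigns the order in which each participant plays the first game on a 1:1 basis".

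On masking there are two sentences. The first is "The experimental and control games are packaged on the screen to protect the blinding at the outset". The second is "However, the video games are not associated with preconceived notions of therapeutic benefit, which minimizes bias".

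The later section on gameplay, test and inquiry repeats the live reading but describes another route to the games: "Each participant will be provided with a link to download the set of video games". The Visit 3 Quantitative Analysis section then compares the PCT Quiz between groups with a t test. No other quantitative measure is planned for comparison between orders.

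**The concern.** Randomizing the order balances participants at the start. It does not protect an outcome that is collected afterwards, face to face on screen, by someone who has just seen which game was played. The packaging on screen stops protecting the blind once the first game opens. The sentence about preconceived notions is most naturally read as concerning participants. Even if it is read more widely, it does not make staff unaware of the order. The Design section has the principal investigator train these staff, and the Hypothesis section predicts a higher score when the Back to Reality Series comes first.

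At stake is the article's own argument that randomization lets quiz differences be attributed to the games. If reading, repeating or explaining an item varies with the order, part of any difference belongs to the administration. No analysis of the quiz scores could separate the two afterwards.

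**Working it through.** **1. Does the text put an informed person at the quiz?**
- Staff stream the games, so whoever streams sees the first game.
- Staff display and read the quiz straight after it, in the same session.
- Masking is claimed at the outset only. The article describes no separate or masked quiz administrator, no self-entry of answers and no automatic scoring.
- Research staff is a pool (students, assistants, a coordinator, per the Design section), and no individual is tied to a task. That the reader knows the order is the natural reading of one continuous Zoom session, but it is not stated.
- If participants download and run the games themselves, staff might see less. The article does not reconcile that route with streaming, and nowhere says that staff are kept unaware.

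**2. The plan's own figures (Visit 3, Sample Size; PCT).** The inputs are a 10-item quiz scored 0 to 10, pilot mean 6.5, SD 1.3 and a target difference of 18%.
- Target: 0.18 × 6.5 = 1.17 points. Standardized: 1.17 / 1.3 = 0.90.
- n per group = 2 × (1.96 + 0.84)² / 0.90² = 19.4, so 20. Two-sided 5% and 80% power are assumed, as the article does not state them. The stated 20 is reproduced.
- With 15% dropout: 20 / 0.85 = 23.5, so 24, as stated.

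**3. What one cue could add.** Assume one cue per participant, in one order only, on an item picked at random, that always turns a wrong answer into a right one. The gain is the chance that the item would otherwise have been wrong.
- At a mean of 6.5/10: 1 − 0.65 = 0.35 points; 0.35 / 1.17 = 30% of the target.
- At the hypothesised mean in the Back to Reality first order, 6.5 + 1.17 = 7.67: 1 − 0.767 = 0.23 points; 0.23 / 1.17 = 20%.

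**4. What a shift of that size would do to the t test.** Assume no true effect, SD 1.3 and a two-sided 5% test (noncentral t). The entries are the chance of a significant result. The number per order is also an assumption, so three values are shown: 20 split in half, the stated 20, and about half of 72 × 0.85 = 61.

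| Assumed shift (points) | 10 per order | 20 per order | 30 per order |
|---|---|---|---|
| 0.25 | 7% | 9% | 11% |
| 0.35 | 9% | 13% | 18% |
| 0.50 | 13% | 22% | 31% |

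The shifts are inputs chosen for illustration. The article gives no figure for cueing.

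**The case against.** The strongest reply is that this is a factual quiz with a fixed key. Each item is displayed as well as read, so every participant sees the same wording, and a rater's judgement hardly enters the score. The article mentions no prompting or clarification. A reading script and session staffing would normally sit in a full protocol or manual, so their absence from an article proves nothing. The project is also framed as a feasibility study.

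Much of this stands. Scoring bias is small, and no defect is claimed from a missing script. What remains is delivery: emphasis, pauses, repeats and answers to queries come before the response is given, and a fixed key does not control them. The article does describe its blinding and its quiz administration, and that stated procedure is what leaves the opening.

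Four stronger readings are tempting and are not supported:
- That the person who streamed the game reads the quiz. This is plausible but not stated.
- That the quiz is the trial's only quantitative outcome. The gameplay survey and the baseline scales are also scored. The quiz is the only one compared between orders.
- That one cued item is worth a full point, 1.0 / 1.17 = 85% of the target. This would need the item to be one that the participant would always have got wrong, whereas the pilot mean implies that about 65% of items are answered correctly without help.
- That bias is present and runs toward the hypothesis. The text supports only that it could.

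**Conclusion.** The point holds as a weakness in how the outcome is collected. The sole quantitative comparison between randomized orders rests on a quiz delivered live by staff who will probably know the order, with no masking stated beyond the outset. The size is unknown. Under the assumption of one perfectly effective cue on a random item, the shift is about 0.35 points (30% of the target), or 0.23 points (20%) at the higher hypothesised mean. With 20 per order and no true effect, 0.35 points would raise the chance of a significant result from 5% to about 13%. Smaller or rarer cueing would matter less, and none at all is possible. The sample size of 20 per group is unaffected. This is a cheap improvement worth making. It does not show that the comparison is invalid.

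**What to change.** Keep the literacy support and standardise it. Show each of the 10 items with a pre-recorded reading, have participants enter their own answers in an online form with automatic scoring, and meet any query only by replaying the recording. State this in the Visit 3 procedures, and reconcile there whether staff stream the games or participants run the download.

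The cost is one recording of 10 items and a short form, with no extra staff and no change in sample size. There are two downsides. Participants lose some live clarification. And because recruitment began in September 2021, a change now would leave two quiz modes in the sample. The order is randomized 1:1 under either mode, so the switch itself does not bias the comparison. Record the mode for each participant and report results by mode as a sensitivity check.

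A second team member who joins after the first game without knowing the order would also serve, but needs extra staff time at every session.
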